**Methods/design:**

This field trial is located at primary care centers. The participants are adults aged 29 to 66 years, with a Body mass Index (BMI) between 29 and 40.99 kg/m^2^ and without diabetes. To date, 245 participants have been assigned randomly to the low-fructose diet intervention group (LFDI) at health centers in the western health service zone of Tenerife island, and 245 to the standard-diet control group (SDC) at health centers in the eastern health service zone. Recruitment is opportunistic and is carried out by physicians and nurses at participating health centers. Initially (baseline), and after 24 weeks of intervention, dietary records, physical activity, waist circumference, BMI, blood pressure, fasting blood glucose and insulin concentrations (HOMA2-IR) and lipid profile are recorded; blood glucose and insulin and lipid profile are also recorded 2 h after a 75-g glucose overload. After 48 weeks (24 weeks after the intervention), fasting blood samples are again obtained and a physical examination is performed. All tests and measures are repeated and recorded except dietary records, physical activity and oral glucose overload. Low-fructose diets are designed by calculating free and total (free + fructose associated with sucrose) fructose contents in standard diets, and removing foods with a fructose content in the highest quartile for the amounts in the standard diet.

Participants in both groups are prescribed a diet that contains 30 to 40% less than the participant’s energy requirements. The primary endpoint is change in HOMA2-IR between baseline and week 24, and other outcomes are change in HDL-cholesterol, LDL-cholesterol, triglycerides , waist circumference to height ratio and BMI. The secondary endpoint is change in HOMA2-IR between week 24 and week 48 together with the outcomes noted above. Comparisons between groups for variables used to indicate IR levels are done with a Student’s *t* test for unpaired variables or the Mann-Whitney *U* test if the distribution is not normal. Multivariate regression models will be used to control for confounding factors not accounted for in the study design, and for independent prognostic factors.

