### Statistical analysis

Before-after changes in IR, laboratory indicators and anthropometric values are determined with Student’s *t* test for paired samples. Comparisons between the intervention and control groups for variables indicative of IR are done with Student’s *t* test for independent samples when the frequency distribution is normal, or with the Mann-Whitney *U* test when the distribution is not normal. For these comparisons multiple linear or regression models are used as appropriate to detect possible confounders or independent prognostic factors for IR that are not controlled for in the trial design. Student’s *t* test for paired samples will be used to analyze changes between week 0 and week 24 in the main outcome variables in each group (HOMA2-IR, fasting blood glucose and insulin, and these same measures after an oral glucose overload) and the secondary outcomes (fasting LDL-cholesterol, HDL-cholesterol and triglycerides, and these same measures after a glucose overload; waist circumference, waist to height ratio, BMI and blood pressure). To verify compliance with the recommended diets the same analysis will be done for total calorie intake and individual nutrient intakes. These analyses will record results for the variables noted above between week 24 and week 48, and between week 0 and week 48. Student’s *t* test for independent samples will be used to analyze the differences between groups observed from week 0 to week 24 for the variables noted above. As potential confounders we will consider calorie intake, variations in nutrient intakes other than fructose, and physical activity. If differences are detected between groups at the start of the study in HOMA2-IR, any nutrient intake or physical activity, appropriate adjustment will be used in the outcomes analysis. An intention-to-treat analysis will be done taking into account losses to follow-up, and using the most recent changes and measurements available for participants who did not complete the study. All hypothesis tests will be two-sided with a significance level of *p* < 0.05, and all statistical analyses will be done with the NT Professional v. 21.0 (IBM) statistical package (SPSS) for PCs in a Windows environment. More specific information about the trial and protocol is summarized in the Standard Protocol Items: Recommendations for Interventional Trials (SPIRIT) Checklist (Additional file 5).

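### Adjustment for baseline HOMA2-IR and the choice of primary test are left to the observed data; the cost is mainly precision and an unfixed effect measure, not type I error

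*Protocol article*

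**What the plan says.** The abstract of the protocol article sets the endpoint: "The primary endpoint is change in HOMA2-IR between baseline and week 24". The Statistical analysis section then gives four instructions that bear on how the arms are compared.

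- **Test chosen by distribution.** For the measures of insulin resistance, an unpaired t test is planned if the data look normal. The alternative is a Mann-Whitney "test when the distribution is not normal". The abstract says the same.
- **Test without that condition.** Later in the same section the t test is named again, "to analyze the differences between groups observed from week 0 to week 24 for the variables noted above", now with no reference to normality. HOMA2-IR is among the variables covered.
- **Conditional baseline adjustment.** The condition reads "If differences are detected between groups at the start of the study in HOMA2-IR". It extends to nutrient intakes and physical activity, and if it is met, some adjustment follows. Neither the criterion for detection nor the form of the adjustment is given.
- **Other covariates.** "As potential confounders we will consider calorie intake, variations in nutrient intakes other than fructose, and physical activity". Baseline HOMA2-IR is not in that list. Regression models are foreseen for confounders and independent prognostic factors, but only where suitable and with no fixed covariate set.

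Under Randomization, the low-fructose diet goes to centers in the western zone and the standard diet to centers in the eastern zone. Similarity of the two populations is assumed.

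**The concern.** Read together, these instructions allow the primary result to be a difference in mean change, a rank comparison, or a baseline-adjusted difference, and the data decide which. These are different effect measures. The Mann-Whitney test cannot carry a baseline term and yields no mean difference.

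Two things are at stake. The first is precision: HOMA2-IR is measured on every participant at week 0, and subtracting it is in general a less efficient use of it than regressing on it. The second is that the primary estimate is not fixed before the data are seen. Both weigh more here because allocation follows geography, so a baseline difference is more plausible than under individual randomization. In addition, the sample size was set on body weight, so the article gives no power for HOMA2-IR.

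**Working it through.** **Inputs.** From the article: 245 per group, 20% loss, two-sided 5% level. Completers: 245 × 0.80 = 196 per group. There is no plan figure to reproduce on this point, because the 245 rests on a 4 kg weight change and no SD or correlation for HOMA2-IR is given. Assumed: baseline-to-week-24 correlation r, equal SD at both visits, and independent participants (no center effect).

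**1. Precision.** With SD = 1, the change score has variance 2(1−r) and ANCOVA has residual variance 1−r². The ratio is (1−r²)/[2(1−r)] = (1+r)/2.

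| r | 2(1−r) | 1−r² | ratio | n per arm matching 196 | ANCOVA power when the change test has 80% |
|---|---|---|---|---|---|
| 0.3 | 1.40 | 0.91 | 0.65 | 128 | 93.5% |
| 0.5 | 1.00 | 0.75 | 0.75 | 147 | 89.9% |
| 0.7 | 0.60 | 0.51 | 0.85 | 167 | 86.0% |
| 0.9 | 0.20 | 0.19 | 0.95 | 187 | 82.0% |

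**2. How often the trigger fires.** Suppose detection means a 5% test on all 245 per arm and the true baseline difference is 0.15 SD. Then 0.15/√(2/245) = 1.66, and Φ(1.66 − 1.96) = 0.38. The difference is flagged about 38% of the time and missed about 62%.

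**3. Type I error when the imbalance regresses to the mean.** A 0.15 SD difference biases the change score by (1−r) × 0.15, which is 0.075 SD at r = 0.5 and 0.045 SD at r = 0.7. Simulated null rejection:

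- change score always used, never adjusted: 11.9% / 8.4% (r = 0.5 / 0.7);
- change score only among trials where the trigger did not fire: about 6.4% / 5.3%;
- the two-step rule as a whole: 5.9% / 5.2%;
- ANCOVA always: 5.1% / 4.7%.

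The middle figures agree with each other. With 196 per arm at both steps the trigger fires 32% of the time, so 0.68 × 6.4% + 0.32 × 5% ≈ 5.9% and 0.68 × 5.3% + 0.32 × 5% ≈ 5.2%. Unflagged trials are those where the observed imbalance happened to be small, so little bias is left in them.

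**4. Type I error when the imbalance is a stable zone difference.** If the 0.15 SD persists unchanged at week 24 with no diet effect, the change score is unbiased. ANCOVA removes only r × 0.15, leaving (1−r) × 0.15 = 0.075 or 0.045 SD. Simulated null rejection at 196 per arm: ANCOVA 13.2% / 9.9%, change score 5.0% / 5.2%.

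**5. Illustration with skewed data.** Assume log-normal HOMA2-IR (log-SD 0.5), balanced groups, and an effect giving 80% power to a change score on the log scale. The planned rule was coded as a baseline test at 5%, then a Shapiro-Wilk check.

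| Analysis | power, r = 0.5 | power, r = 0.7 |
|---|---|---|
| Planned two-step rule | 73.4% | 73.6% |
| ANCOVA, raw scale | 84.5% | 78.2% |
| ANCOVA, log scale | 90.0% | 86.4% |

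The planned rule ended in Mann-Whitney in about 94% of these trials. Part of the gain comes from the baseline term and part from the log scale.

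**The case against.** Five things can be said for the plan.

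- **Adjustment is already foreseen.** The section and the abstract both plan regression models for confounders and prognostic factors, and baseline HOMA2-IR could enter as one. This stands in part: the plan does not exclude adjustment, but it does not commit to it or fix the covariates.
- **No significance test is prescribed at baseline.** Correct; the text speaks only of differences being detected. The 38% assumes a 5% test. Any detection rule still makes the model depend on the data.
- **The error rate is sound.** A reader might infer from the 8-12% rejection of an unadjusted change score that the planned rule inflates type I error to that level. The calculation does not support this: that rate belongs to a plan that never adjusts, and the two-step rule stays at about 5-6%.
- **ANCOVA is not simply better here.** This is the strongest point and it stands. With allocation by zone, a baseline difference may be stable rather than chance, and then ANCOVA is the biased analysis. The article cannot settle which case holds.
- **The endpoint is change, and skewness is not documented.** On the raw scale, the arm coefficient is the same whether week-24 value or change is the outcome once baseline is in the model, so the endpoint is kept. A log scale would replace it with a relative effect and needs its own justification.

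**Conclusion.** The point holds as a matter of a primary comparison that is not fixed and of precision that may be lost. The article itself states both data-driven rules and states the between-group test in two ways, so this is not detail left to an unseen analysis plan.

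The gain from always adjusting depends on r, which the article does not give. At r of 0.5 to 0.7, an unadjusted change score needs 33% to 18% more patients for the same precision (1/0.75 and 1/0.85). All figures ignore clustering within the 16 centers. No material type I inflation is claimed for the two-step rule when the imbalance regresses to the mean. Nor does the article support the claim that baseline adjustment makes the arms comparable: neither ANCOVA nor the change score removes confounding by zone. This is an improvement that should be made, not a flaw that invalidates the trial.

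**What to change.** Pre-specify one primary model: week-24 HOMA2-IR on arm, with baseline HOMA2-IR always included and any further baseline covariates listed by name. If skewness is expected, choose the log scale in advance and report the ratio of geometric means with a 95% CI. Delete the baseline-difference trigger and the normality switch, and reconcile the two statements of the between-group test.

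Name the unadjusted change-score comparison as a sensitivity analysis, report both results, and state that neither removes zone confounding. If they disagree, the disagreement itself shows that the answer depends on whether the west-east baseline difference is stable.

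The cost is wording only, since baseline HOMA2-IR is already collected on everyone and the article describes the trial as ongoing. The downside is the ANCOVA bias under a stable zone difference, which is why the sensitivity analysis must be named beforehand and not added afterwards.

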## Methods/design

The *primary objective* of this study is to determine whether decreasing the consumption of foods rich in fructose or sucrose leads to a decrease in IR after 24 weeks in a population with obesity, independent of a reduction in calorie intake.

The *secondary objective* is to determine whether after 48 weeks (24 weeks after the end of the intervention according to protocol), IR levels remain unchanged compared to the end of the 24-week intervention period.

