### Design

A single-blind, multicenter, randomized controlled **f**ield trial with two groups of participants (low fructose/sucrose diet versus standard diet) recruited at primary care health centers in Tenerife island (Canary Islands, Spain). Sample size: because of the lack of consensus in the academic literature regarding the cutoff value of HOMA2-IR that defines the presence of IR, we opted to use body weight change. We estimated a mean weight loss of 4 kg (1.43 kg/m^2^ BMI assuming a mean height of 1.67 m for the Canary Islands’ population [16]), a significance level of *p* ≤ 0.05, 80% power and a 20% dropout/loss to follow-up rate. A weight loss of 4 kg was estimated based on maximum weight loss in the only interventional trial reported to date of the effect of lower fructose consumption on body weight and IR [15]. Dietary intervention trials aimed at studying weight loss have reported similar amounts of weight loss after 6 months [17]. In the trial reported here, in which both groups consume an isocaloric diet, we do not anticipate differences between the groups in the amount of weight lost. Based on these calculations our estimated sample size for each of the two groups is 245 participants.

The primary outcome measure is insulin resistance (IR) which is estimated from fasting serum glucose and insulin concentrations with the computer-based Homeostasis Model Assessment system (HOMA2-IR) at baseline, 24 and 48 weeks. The secondary outcomes are BMI, waist circumference (waist to height ratio) and blood pressure which are measured at baseline, 4, 8, 12, 16, 20, 24 and 48 weeks, and total cholesterol, HDL-cholesterol, LDL-cholesterol and triglycerides which are measured at baseline, 24 and 48 weeks.

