
### Intervention

All participants sign an Informed Consent Form. The study was approved by the Ethics Committee of Nuestra Señora de La Candelaria University Hospital. The intervention (except for nutrition counseling), number of appointments and laboratory tests are the same in both groups.

Participants in the LFDI group are advised to eat a low-fructose diet designed on the basis of standard diets (1000, 1250, 1500, 1750, 2000, 2250, 2500 or 2750 kcal/day) recommended by the Canary Islands Health Service [18]. Low-fructose diets are designed by calculating free and total (free + fructose associated with sucrose) fructose contents in standard diets. Foods with a fructose content in the highest quartile for the amounts corresponding to the standard diet are removed from the standard diet. The format and graphical appearance of the information about the participant’s diet are identical in both groups. Physicians and nurses who prescribe the standard diets are unaware of which foods have been excluded from the low-fructose diets. To avoid contamination bias while recruitment is currently underway, the present report does not include information on the composition of the low-fructose diets.

Nutrition counseling and reinforcement take place at weeks 2, 4, 8, 12, 16 and 20. During this process we emphasize to participants the importance of involving in the intervention the person in the household who purchases and/or prepares food. At week 2, after the physician or nurse has reviewed the nutritional information, intervention via individualized nutrition counseling begins. At week 24 a second blood sample is obtained for analysis. Two weeks before week 24 the participants are given a new Information Pack containing the same materials as the initial Information Pack at the start of the study, with instructions on how to record foods and beverages consumed during 4 days (including one weekend day or holiday). On the day of the appointment to provide a new blood sample, the participant meets first with the physician or nurse to review their food diary in detail.

The schedule of enrollment, interventions and assessments, which is based on the Standard Protocol Items: Recommendations for Interventional Trials (SPIRIT) figure, is shown in Fig. 1 and the process for participant recruitment and follow-up is shown in Fig. 2.

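### Carrying the last value forward gives every participant lost before week 24 a HOMA2-IR change of exactly zero, which dilutes the primary comparison and, if dropout differs between arms, can create a false difference

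*Protocol article*

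**What the plan says.** The only rule for incomplete follow-up is in Statistical analysis: "An intention-to-treat analysis will be done taking into account losses to follow-up", "using the most recent changes and measurements available for participants who did not complete the study". No other missing-data method and no other analysis set is named.

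The Design section gives the timing of the primary outcome as "HOMA2-IR) at baseline, 24 and 48 weeks". The Intervention section confirms that no blood is drawn in between: "At week 24 a second blood sample is obtained for analysis". BMI, waist circumference and blood pressure differ, being "measured at baseline, 4, 8, 12, 16, 20, 24 and 48 weeks".

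The primary endpoint is the change in HOMA2-IR from baseline to week 24. The secondary endpoint is the change from week 24 to week 48, and the secondary objective (opening of Methods/design) is to determine whether "IR levels remain unchanged compared to the end of the 24-week intervention period". Design plans 245 participants per arm, 80% power and 20% loss. Both arms receive a calorie-restricted diet and are expected to lose similar weight (Design, Discussion).

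**The concern.** Carrying a value forward has some basis when there are interim measurements close to the missing one. For HOMA2-IR there are none. For anyone who leaves before week 24, the most recent value is the baseline value, so the rule records no response to 24 weeks of diet. For anyone who leaves after week 24, the week-24 value stands in for week 48, so the rule records no change over the period in which the secondary objective asks whether change occurred.

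Two things are at stake. The treatment contrast is diluted by the dropout fraction. Also, because both arms are expected to improve, entering zeros penalises whichever arm loses more people, so a difference in retention can appear as a difference in diet effect. In both cases the imputed zeros enter the t test as if they had been observed.

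**Working it through.** **Inputs from the protocol article.** 245 per arm, 20% loss, 80% power (Design); two-sided 0.05 (Statistical analysis).

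**Assumed, because the article gives no effect or SD for HOMA2-IR.** Changes are in SD units with SD 1. The common improvement M is 0.5 to 1.0 SD. The dropout splits are 15% vs 25% and 10% vs 30%. Dropout is unrelated to outcome within an arm.

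**The plan's own figure.** The 245 rests on a 4 kg weight loss with no stated SD, so it cannot be reproduced. Read as a two-group comparison of means with 245 × 0.8 = 196 evaluable, it implies an SD of 14.13 kg. That does not affect this point. The standardised difference detectable with 196 per arm is (1.96 + 0.842) × √(2/196) = 0.283, used below as the true effect.

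**Step 1, who gets a zero.** 0.20 × 245 = 49 participants per arm.

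**Step 2, equal dropout.** With dropout r in both arms the expected difference is (1 − r) × true difference: 0.8 × 0.283 = 0.226. Simulation (5,000 trials, M = 0.5) gave 0.225 with 76% power under carry-forward, against about 80% for observed cases. With no true effect, type I error stayed near 5%.

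**Step 3, unequal dropout, no true effect.** If both arms truly improve by M, the expected false difference is M × (gap in dropout rates). The variance of the imputed change in an arm is (1 − r) + r(1 − r)M². The standard error is √[(V₁ + V₂)/245].

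| Dropout, LFDI vs SDC | M | V₁ + V₂ | SE | False difference | Type I error |
|---|---|---|---|---|---|
| 15% vs 25% | 0.5 | 0.882 + 0.797 | 0.0828 | 0.05 | 9.3% |
| 15% vs 25% | 1.0 | 0.978 + 0.938 | 0.0884 | 0.10 | 20.5% |
| 10% vs 30% | 0.5 | 0.923 + 0.753 | 0.0827 | 0.10 | 22.7% |
| 10% vs 30% | 1.0 | 0.990 + 0.910 | 0.0881 | 0.20 | 62.2% |

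Simulation agreed where run (9%, 23% and 62% for rows 1, 3 and 4). Observed-case analysis stayed at about 5% throughout.

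**Step 4, unequal dropout, true effect −0.283, SDC change −0.5.** With 30% lost in LFDI and 10% in SDC: 0.7 × (−0.783) − 0.9 × (−0.5) = −0.098, and simulated power is 22%. With the rates reversed: 0.9 × (−0.783) − 0.7 × (−0.5) = −0.355, an overstatement. The bias can run either way.

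**Step 5, weeks 24 to 48 within an arm.** For a true change of 0.20 SD with 20% missing, the carried-forward mean is 0.8 × 0.20 = 0.16. Its variance is 0.8 + 0.16 × 0.04 = 0.806, so the SE is √(0.806/245) = 0.0574. The observed-case SE is 1/√196 = 0.0714. The ratio is 0.80, so the interval is about 20% too narrow and centred too near zero. The test statistics are almost equal (0.16/0.0574 = 2.79 and 0.20/0.0714 = 2.80), and both reject about 80% of the time.

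**Step 6, dropouts who differ from completers.** If dropouts rebound by 0.5 SD and completers by 0.1 SD, the true mean is 0.8 × 0.1 + 0.2 × 0.5 = 0.18. Carry-forward gives 0.8 × 0.1 = 0.08 and completers alone give 0.10.

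**The case against.** **Nothing predicts unequal dropout.** Design gives a single 20% rate, and Intervention says that appointments and laboratory tests are the same in both arms. This stands: the dropout gap is an assumption, as is the size of the common improvement, and the 62% figure takes the extreme of both. Allocation by health zone makes unequal retention possible, since the arms differ in centers and staff, but the article does not forecast it. At equal dropout the error is toward no difference, and the loss of power is modest.

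**Zero may be roughly right for dropouts.** If those who leave return to baseline, a zero change is close to the truth. This also stands as a possibility, and the dilution to 80% holds only if dropouts would have changed as completers did. It is a reason to examine the assumption in a sensitivity analysis, not to fix it in the main one.

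**The rule carries changes as well as measurements.** A participant with only a baseline value has no earlier change to carry, so the zero still follows.

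**The intention-to-treat analysis is not labelled primary.** That is so, but it is the only analysis set named.

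**A stronger reading of the secondary objective.** A reader might infer that the rule decides that objective in advance. It does so for each imputed participant but not for the group: step 5 shows that the paired test rejects about as often as it would on observed cases. Nor does the article state an equivalence claim. Its objective is to determine whether IR is unchanged, and its endpoint is the change itself.

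**Conclusion.** The rule does not suit the HOMA2-IR schedule and should be replaced. That each early dropout gets a zero change follows from the article's text alone. At equal 20% dropout the cost is an effect shrunk to 80% and power of about 76% instead of 80%, assuming dropouts would have changed as completers did. For weeks 24–48 it is a mean shrunk to 80% with an interval about 20% too narrow.

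The inflated type I error (about 9–20%, or 23–62% with the wider gap) is conditional on both an assumed dropout gap and an assumed common improvement of 0.5–1.0 SD. A reader might infer that the primary result is bound to be falsely positive. The article does not support that, because equal dropout leaves type I error near 5% and unequal dropout can favor either arm.

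The zero-change argument does not extend to BMI, waist circumference or blood pressure, which have 4-weekly values. A participant who misses week 24 but attends week 48 is not clearly covered by the rule.

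A minor and separate inconsistency concerns the week-48 variable list. Statistical analysis states "These analyses will record results for the variables noted above between week 24 and week 48", and that list includes post-overload measures and nutrient intakes. The Abstract says of week 48: "All tests and measures are repeated and recorded except dietary records, physical activity and oral glucose overload". No HOMA2-IR result depends on this.

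**What to change.** - **Main analysis.** Analyse HOMA2-IR at weeks 0, 24 and 48 with a likelihood-based repeated-measures model, taking the arm-by-time contrast at week 24 as the primary estimate. Any center effect should be random, because centers are nested in arm through the health zones and fixed center effects would be confounded with arm. The alternative is multiple imputation with the 4-weekly BMI, waist circumference and blood pressure as auxiliary variables.
- **Sensitivity analyses.** Keep carry-forward only here, and add one analysis for data not missing at random.
- **Secondary objective.** Report the week 24–48 change with its confidence interval, and do not read a non-significant paired t test as showing no change. With 196 observed per arm the 95% half-width is about 1.96 × 0.0714 = 0.14 SD, so a non-significant result is compatible with some rebound. If a margin is used, it must be a fixed HOMA2-IR value set before the data are seen, not a fraction of the observed week-24 effect.
- **Week-48 list.** Remove the post-overload and dietary-intake variables from the week 24–48 and week 0–48 analyses.

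The cost is revised analysis wording and modest programming, with no new data. The main analysis would then rest on a missing-at-random assumption, which the added sensitivity analysis is there to test.
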